### Outcomes

#### Primary outcomes: screening and brief advice rates

PHCUs will be asked to screen all patients aged 18 years and over who attended the PHCU. These patients are defined as eligible patients.

Patients will be screened for hazardous and harmful alcohol consumption with AUDIT-C [32]. Screen positives, or at risk patients, are defined as those who scored ≥ 5 for men or ≥ 4 for women on AUDIT-C. Participating staff that have signed up to the study will be asked to deliver brief alcohol advice of 5 to 15 min duration to at-risk patients, with the length and format of the brief advice based on country-specific guidelines or, for Poland where national guidelines are lacking, the European guidelines developed by PHEPA [33]. Providers of PHCUs allocated to e-BI activity will be asked to refer patients to a computerized brief advice program, considered equivalent to providing brief advice. Besides counting referral rate to e-BI, actual e-BI log-in rates of patients will be collected.

Screening and brief advice will be measured at five timepoints: during the four-week baseline period, the three consecutive four-week blocks during the twelve week implementation period; and, the four-week follow-up period, which will occur during the seventh month after the end of the twelve-week implementation period using paper tally sheets, with the exception of Catalonia who will use their electronic patient records. The tally sheets include AUDIT-C scores (*i.e.*, identification of at risk patients) with additional table to indicate the type of brief advice that was delivered to the patients at risk. Gender and age of patients will be recorded as well as the name and profession of the provider.

The screening rate will be calculated as the number of completed screens divided by the total number of consultations of all patients eligible for screening (as defined above) per participating provider times 100. The brief advice rate will be calculated as the number of BIs delivered (received oral brief advice, and/or were given an advice leaflet, and/or were referred to the e-BI program, and/or were referred to another provider in or outside the practice), divided by the total number of screen positives per participating provider times 100. Information will also be collected on the number of screen negatives who received brief advice.

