### Statistical methods

Because of the hierarchical structure of the data (individual providers nested within PHCU nested within country), we will perform multilevel analyses of the screening and advice rates to examine the effect of the implementation strategies in comparison with the controls. The intention to treat analyses will include all participating providers (see above). Per protocol analyses will include only actively participating providers (see above). In all the analyses, we will use exposure to the implementation strategy as co-variate. Exposure is defined as positive if the providers meet the following criteria: financial—the PHCU received the financial reimbursement; e-BI—the provider handed out at least one referral card; and T&S—the provider attended the two face-to-face educational meetings. If these criteria will not be met, the exposure will be defined as negative.

Analyses will be performed in SAS V9.2 and based on mixed effects model (PROC GLIMMIX and PROC MIXED). We will use a random intercept model with fixed variables.

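### Exposure after allocation is a covariate in every planned analysis, intention-to-treat included, so no described model estimates the randomised effect; the fault is most direct for e-BI and the brief advice rate

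*Protocol article*

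**What the plan says.** All the analysis text is in the Statistical methods section of the protocol article.

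- The stated purpose is "to examine the effect of the implementation strategies in comparison with the controls".
- Two analysis sets are defined. "The intention to treat analyses will include all participating providers", whereas the per-protocol set is limited to active participants: "Per protocol analyses will include only actively participating providers (see above"). The two differ only in which providers are included.
- One covariate rule then covers both: "In all the analyses, we will use exposure to the implementation strategy as co-variate".
- Exposure is positive under T&S if the provider attended both face-to-face meetings, under financial reimbursement if the PHCU was paid, and under e-BI by this rule: "e-BI—the provider handed out at least one referral card". Otherwise it is negative.

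Two other places bear on these definitions. Under Primary outcomes, the numerator of the brief advice rate includes patients who "were referred to the e-BI program", and such a referral is treated as equal to giving brief advice. Table 1 says that reimbursement is paid for registered screening and brief intervention activity.

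The Aim and objectives section asks what happens when training, payment or a referral option is provided to PHCUs. That is a question about the effect of allocation.

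**The concern.** Intention-to-treat needs two things: providers analysed in the groups to which their PHCU was randomised, and no adjustment for anything that allocation may have influenced. The plan secures the first and gives up the second. Exposure can be positive essentially only where the strategy was allocated. Within those arms it separates providers by what they did afterwards, so conditioning on it breaks the comparability that randomisation created.

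The three exposures do this in different ways:

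- **e-BI.** The covariate is a function of the brief advice outcome: a provider with no advice recorded cannot be exposed.
- **T&S.** Attending both meetings is provider behaviour. It biases the comparison to the extent that keener providers both attend more and screen more.
- **Financial.** Payment is set at PHCU level. It may almost coincide with allocation, or it may depend on the activity being measured.

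At stake is the main comparison for both primary outcomes. A strategy without effect could appear harmful on one coefficient and strongly beneficial on the other, and a real effect could be missed or change sign.

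**Working it through.** **1. What the sample size assumes.** The Sample size section gives 8% to 12% for screening, 4% to 6% for brief advice, ICC 0.029, 1,000 patients per PHCU, 80% power and alpha 5% (two-sided assumed). The design effect is 1 + 999 × 0.029 = 29.97. With a continuity-corrected comparison of two proportions, four groups against four:

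- Screening: 932 per side × 29.97 / 1,000 = 27.9 PHCUs per side, or 55.9 in all. Rounded up to a multiple of eight this is 56, as stated.
- Brief advice: 1,962 × 29.97 / 1,000 = 58.8 per side, or 117.6 in all. Rounded up this is 120, as stated.

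The stated figures therefore reproduce as a comparison of PHCUs as allocated. Exposure plays no part in them.

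**2. What the coefficients mean.** Take one strategy and fit rate = a + b × allocation + c × exposure, with exposure zero in controls. There are only three cells, so by least squares:

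- b = mean of non-exposed strategy-arm providers minus mean of controls;
- c = mean of exposed minus mean of non-exposed providers, within the strategy arm;
- randomised difference = b + (share exposed) × c.

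The randomised effect is split over two coefficients, and neither is that effect. If exposure replaces allocation, its coefficient compares exposed providers with a mixture of controls and non-exposed strategy-arm providers, which is an as-treated contrast.

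**3. e-BI and brief advice by hand.** Let p be the chance that a screen-positive patient receives advice, and q the share of advice given by card. Among providers with no card, and ignoring variation between PHCUs, the expected rate is p(1 - q) / (1 - pq). With no effect, p = 4% in both arms:

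- q = 0.3: 0.028 / 0.988 = 2.8%, so b = -1.2 points;
- q = 0.6: 0.016 / 0.976 = 1.6%, so b = -2.4 points;
- q = 1: 0%, so b = -4.0 points.

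**4. The same by simulation.** Assumed, not in the article: 60 against 60 PHCUs for e-BI alone, 5 providers per PHCU, 20 screen positives per provider, and PHCU rates varying with ICC 0.029. There were 300 runs per row, with standard errors clustered on PHCU.

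| True rates | q | Allocation only | b with exposure added | Rejection on b | c | Share exposed |
|---|---|---|---|---|---|---|
| 4% v 4% | 0.3 | 0.02 | -1.50 | 74% | 7.70 | 0.20 |
| 4% v 4% | 0.6 | -0.01 | -2.75 | 100% | 8.07 | 0.34 |
| 4% v 4% | 1.0 | -0.04 | -4.03 | 100% | 8.36 | 0.48 |
| 4% v 6% | 0.3 | 1.89 | -0.68 | 17% | 9.37 | 0.27 |
| 4% v 6% | 0.6 | 1.95 | -2.42 | 100% | 9.80 | 0.44 |
| 4% v 6% | 1.0 | 2.02 | -4.01 | 100% | 10.22 | 0.59 |

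The identity in step 2 holds: in the third row, -4.03 + 0.48 × 8.36 = -0.02. Allocation alone rejects in 5-6% of null runs. Exposure alone, in place of allocation, gives +5.7 to +6.9 points under no effect, significant in all runs. The b values lie below those of step 3 because variation between PHCUs makes providers without a card more often members of low-rate PHCUs.

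**5. T&S and screening by simulation.** Assumed: 60 against 60 PHCUs, 6 providers each, logit-scale SD 0.6 (PHCU) and 1.0 (provider), control screening about 8.4%, about 60% exposed, no true effect. The attendance link is in logits per SD of provider propensity.

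| Link | b with exposure added | False rejection on b |
|---|---|---|
| none | about 0 | 2-4% |
| weak (0.25) | about -1.1 points | 17-18% |
| moderate to strong (0.5-1.0) | about -2 to -3.4 points | about 45-93% |

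Adding the provider's baseline rate reduces false rejection to 4-13% if propensity is stable, but leaves 19-87% if propensity correlates only 0.7 with baseline.

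**6. Not simulated.** Financial exposure, and e-BI exposure in the screening model. No size is claimed for either.

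**The case against.** The wording of the rule is not in dispute, but five limits on its consequences are fair.

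- **Model form.** The article specifies a random intercept model with fixed variables and does not say whether exposure joins allocation or stands in for it. Statements about an allocation coefficient are therefore conditional. This stands, but the other reading is as-treated and no closer to intention-to-treat.
- **Reach of the outcome argument.** A reader might infer that e-BI exposure is an outcome event for both primary outcomes. The definitions support that only for the brief advice rate. For the screening rate the link is indirect: a card follows a positive screen, so providers who screen more have more chances to hand one out.
- **Financial exposure.** A reader might infer the same motivation bias here. The article does not support that. If nearly every PHCU in these arms is paid, exposure copies allocation and the trouble is collinearity. If payment fails where nothing is registered, exposure depends on the outcome. The text does not settle which.
- **Size.** A reader might infer that false positives are near certain. They are not. With no link between attendance and motivation, T&S shows no bias, and for e-BI the rejection rate at a 30% card share is 74%. The simulations use one strategy, one period and clustered least squares, whereas the plan has mixed models and five measurement periods.
- **Baseline adjustment.** It could remove much of the T&S bias if provider propensity is stable. The article does not state such adjustment, and it would not cure an e-BI covariate built from the outcome.

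Deferral to a fuller analysis plan is no answer, because the article itself fixes the rule and the definitions.

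**Conclusion.** Wrong as written. No described analysis estimates the effect of allocation that the hypotheses ask about and the sample size is built on. This follows from the text and the algebra in step 2 and does not depend on a simulation.

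The degree of harm differs by strategy and outcome:

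- **e-BI, brief advice rate:** bias follows from the definitions. With exposure added and no effect, the allocation coefficient is about -1.5 to -4.0 points for card shares of 30-100%, with 74-100% false rejection. With a true gain of 2 points it is about -0.7 to -4.0. The sign at a 30% share depends on variation between PHCUs: without it, 0.042 / 0.982 = 4.3% against 4% gives +0.3.
- **T&S:** false rejection is nominal, about 17-18%, or about 45-93% for no, a weak, or a moderate to strong link between attendance and motivation.
- **e-BI in the screening model, and financial exposure:** the objection in principle holds, but the size is unknown.

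All sizes are illustrative. Providers per PHCU, screen positives per provider, card share, exposed share and the attendance link are assumptions.

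**What to change.** Limit the covariate rule to secondary analyses. State that the primary intention-to-treat models for screening rate and brief advice rate use the allocated strategy indicators (T&S, financial reimbursement, e-BI), keep the planned multilevel structure and contain no exposure term.

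Any exposure analysis should be secondary and labelled as a non-randomised comparison. If a complier-average analysis with allocation as instrument is preferred, state its assumptions, in particular that allocation acts only through exposure. Colleagues who share a PHCU may break that assumption. Do not use referral-card exposure to explain the brief advice rate. Handing log-in cards to providers would not be a good substitute definition: the article does not list it as recorded, and it would nearly duplicate allocation.

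The cost is a change of wording. No new data are needed, and the 56 and 120 PHCUs are unaffected, because that calculation already compares PHCUs as allocated.

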## Discussion

By conducting this trial, we are trying to address the well-known implementation gap (evidence to practice) of screening and brief interventions for hazardous and harmful alcohol consumption in PHC. For example, researchers rarely have been in a position to actively compare a number of incentive-based strategies. With this trial, we aim to assist in building a knowledge base, on which policy could be based on.

We are aware of some strengths and limitations of this trial. This trial is approached pragmatically. In other words, each of the five countries differs slightly in the implementation strategy contents. For example, countries will differ in their distribution of research fees, amount of financial reimbursements, and deliverers of training and support strategies. The research team explicitly determined this pragmatic approach, because they considered this approach being most valuable for country policy makers. Albeit, in terms of research, this is less powerful because there are small variations in implementation strategies per country.

The five participating countries are different in their organization of primary care and have different drinking patterns. This creates opportunities to conduct across-country analyses and relate different implementation rate outcomes to cultural and organizational differences. These results can consequently be applicable through Europe and other similar Western countries. In the future, if our implementation strategies result in improved screening and brief intervention rates, other countries with comparable primary care systems could use these strategies to improve the prevention of hazardous and harmful alcohol consumption in their country.

## Abbreviations

e-BI: Internet based brief interventions; PHC: Primary healthcare; PHCU: Primary healthcare unit; SAAPPQ: Short Alcohol and Alcohol Perceptions Questionnaire; T&S: Training and support.
